## Abstract

**Background:**

No treatment has convincingly been proven to be beneficial for microvascular obstruction (MVO) in patients with ST-elevation myocardial infarction (STEMI). Several studies have described the effects of Danhong Injection. However, evidence of a rigorously designed verification study is still lacking, and the intervention timing of Danhong Injection is uncertain.

**Methods:**

The DIRECTION study is a multicenter, prospective, randomized, evaluator-blind study. A total of 336 patients with STEMI receiving percutaneous coronary intervention (PCI) will be randomly assigned to conventional treatment, the preoperative Danhong Injection, or the postoperative Danhong Injection. The primary outcome is rate of ST-segment resolution (STR) ≥ 70% at 90 min after PCI. The secondary outcomes are the degree of STR, Thrombolysis in Myocardial Infarction (TIMI) flow grade, TIMI myocardial perfusion grade, left ventricular ejection fraction, N-terminal prohormone brain natriuretic peptide, high-sensitivity C-reactive protein, and infarct size expressed as area under the curve for cardiac troponin I (cTnI) and for creatine kinase MB. The major adverse cardiovascular events and hospital readmission events will be recorded. Health quality will be assessed with the 12-item Short Form Health Survey. The safety outcomes include bleeding events, adverse events, and abnormal changes in routine blood tests. Psychological status and dietary patterns will be evaluated using Hamilton Depression Rating Scale and Food Frequency Questionnaire as the relevant indicators.

**Discussion:**

This trial will evaluate the efficacy and safety of Danhong Injection, as well as its optimal timing of intervention to prevent MVO in patients with STEMI.

**Trial registration:**

Chinese Clinical Trial Registry, ChiCTR1900021440. Registered on February 21, 2019.

## Background

It is well known that myocardial infarction (MI) is associated with high mortality rates [1, 2]. According to the data of the China Cardiovascular Disease Report 2017 Summary, the mortality of acute myocardial infarction (AMI) in China is on the rise [3]. Prompt induction of complete and sustained infarct-related artery recanalization is paramount, and primary percutaneous coronary intervention (PCI) is currently the treatment of choice [4]. However, a significant proportion of patients still face low or no reperfusion at the myocardial tissue level, even though the infarcted blood vessels have been recanalized [5]. The incidence of slow or no reperfusion was 5–60%, depending on the study population, evaluation method, and time [6, 7]. The occurrence of slow or no reperfusion/microvascular obstruction (MVO) was associated with a lower ejection fraction, increased ventricular volumes and infarct size, and a greater risk of major adverse cardiac events (MACE), which severely affected the prognosis of patients who have had an MI.

MVO after PCI is a dynamic process involving multiple pathophysiological mechanisms [8]. The underlying pathological mechanisms are now known to include injury related to ischemia, reperfusion, endothelial dysfunction, and distal thromboembolism [6]. The complexity makes it not an ideal or standard treatment currently [9]. Different treatments have been tried, including thrombus aspiration and distal protective devices that can filter microemboli [9] and drug therapies such as vasodilators [10, 11], calcium channel blockers [12], nicorandil [13], cyclosporine A [14], platelet glycoprotein IIb/IIIa receptor antagonist [15], and glucagon-like peptide-1 analog [16]. There is currently experimental evidence that abciximab, adenosine, nicorandil, and nitrate are beneficial in reducing the incidence of no-reflow, but the clinical evidence is limited [17]. It is known that a traditional Chinese medicine (TCM) compound can interfere with the complicated pathological changes of the body for multitarget interactions [18]. In recent years, some clinical experimental studies have demonstrated the efficacy of TCM intervention in MVO and reperfusion injury after MI, revealing its unique advantages and potential application value in this field.

Danhong Injection is a TCM compound preparation extracted from *Salvia miltiorrhiza* and safflower [19]. It has the functions of promoting the blood circulation and clearing the vessels. The major active ingredients are tanshinone, salvianolic acid, safflower yellow pigment, phenol glycosides, and catechol. Danhong Injection has been widely applied in the treatment of coronary heart disease, angina pectoris, MI, pulmonary heart disease, and cerebral infarction since it was launched in the Chinese market in 2003. A recent systematic review showed that Danhong Injection significantly reduced the risk of death and recurrent angina, arrhythmia, and heart failure and improved left ventricular ejection fraction (LVEF) and reperfusion in patients with AMI [20]. Compared with PCI alone, Danhong Injection combined with PCI can improve vascular endothelial function, reduce inflammation, and prevent platelet aggregation, suggesting that it may act on multiple pathological steps, improve myocardial microcirculation, and reduce reperfusion injury [21]. Several small-sample clinical trials demonstrated that Danhong Injection can reduce the occurrence of coronary no-reflow (Thrombolysis in Myocardial Infarction [TIMI] blood flow grade < 3 or corrected TIMI frame count >40s) in patients with MI and can promote postoperative microcirculation recovery (ST-segment resolution [STR] ≥ 70% or 50%) [22–24]. However, limited research quality with the varieties of intervention timing and indicators makes it hard to come to a solid conclusion. More rigorously designed research and verification studies with a sufficient number of patients are warranted.

## Methods

### Purpose and study design

The purpose of this study is to assess whether additional Danhong Injection treatment started before or after PCI is superior to standard treatment alone for the prevention of MVO in patients with ST-elevation myocardial infarction (STEMI). The research is designed as a multicenter, prospective, stratified, block-randomized, evaluator-blind study being conducted within China from 1 May 2019 to 30 May 2020. A flowchart of the study is shown in Fig. 1. The enrollment of patients will take place from 1 May 2019 to 30 April 2020, and the observation period is 1 month. Central ethical approval has been confirmed by the Research Ethics Committee of Dongzhimen Hospital Affiliated to Beijing University of Chinese Medicine (ref. approval no. DZMEC-KY-2019-03). The trial was registered in the Chinese Clinical Trial Registry (ChiCTR1900021440). Reporting of the protocol follows the Standard Protocol Items: Recommendations for Interventional Trials (SPIRIT) statement (checklist uploaded as Additional file 1).

**Fig. 1 Fig1:**
[figure not shown]
DIRECTION (Danhong Injection before or after percutaneous coronary intervention) trial protocol flow diagram

### Patient recruitment and eligibility

Patients will be screened for eligibility at hospital admission as soon as possible. Patients will be eligible if they meet the following criteria:
Diagnosed with STEMI according to the fourth edition of the 2018 European Society of Cardiology (ESC) General Definition of Myocardial Infarction [25] and the 2018 ESC Guidelines for Acute ST-Segment Elevation Myocardial Infarction [26]Show symptoms of myocardial ischemia within 12 hHave direct PCI surgery indications and accept stent placement in infarct vesselsBoth men and women aged between 18 and 75 yearsAgree to participate in the research and sign the informed consent form

The exclusion criteria are as follows:
Received thrombolytic therapy before PCICardiogenic shock, heart rupture, or ventricular septal perforationCardiopulmonary resuscitation ≥20 minActive hemorrhage or sensitive to hemorrhageTarget vessel received stent implantationHaving an implantable cardiac defibrillator or pacemakerCombined with severe liver, kidney, or hematopoietic system diseases or malignant tumorsAllergic to the experimental drugsPatients with major mental illnesses that make it difficult for them to cooperateKnown pregnancy or lactationAcute pericarditis, subacute infective endocarditis, and/or aortic dissectionLeft bundle branch blockLife expectancy ≤12 monthsParticipation in another clinical study with an investigational product or device during the last 30 days or during the study

### Intervention

Patients will receive aspirin 300 mg and clopidogrel 600 mg (or ticagrelor 180 mg) before PCI. Postoperative treatments will include antithrombotic medication (aspirin 100 mg daily with clopidogrel 75 mg daily or ticagrelor 90 mg twice daily), anti-myocardial ischemia (β-blockers, nitrates, calcium antagonists), inhibition of cardiac remodeling (angiotensin-converting enzyme inhibitor, angiotensin receptor blocker, aldosterone receptor antagonist), and lipid control (atorvastatin 20 mg daily). These are all serving as conventional treatment for patients with STEMI. Patients in the preoperative-Danhong group will additionally receive Danhong Injection treatment (40 ml with 250 ml of saline, intravenous drip infusion) as early as possible before PCI and continue to the seventh day, once per day. Patients in the postoperative-Danhong group will additionally receive Danhong Injection treatment (40 ml with 250 ml of saline, intravenous drip infusion) right after PCI and continue to the seventh day, once per day.

It should be noted that any Chinese medicine related to the treatment of coronary heart disease should not be taken orally, intravenously, or intracoronally during the study. According to the hospital centralized monitoring data [27], the following drugs should be avoided in combination with Danhong Injection: potassium magnesium aspartate, thymosin, celecoxib, and bisoprolol fumarate. The patients will stay in the hospital during the intervention period, which is convenient to monitor adherence to the intervention.

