### Sample size

Based on the results of the previous investigation [31–33], a sample size of 336 participants was estimated to provide 80% power to detect an absolute difference of 20.2% between the combined Danhong group and control in the rate of STR ≥ 70% measured at 90 min after PCI at a two-sided significance level of 0.05, assuming an STR ≥ 70% rate of roughly 50% for the control group and 20% loss to follow-up.

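### Use of Danhong before randomisation is neither excluded nor addressed, so the efficacy and timing contrasts could be diluted to an unknown degree

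*Protocol article*

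**What the plan says.** The Intervention section states that "any Chinese medicine related to the treatment of coronary heart disease should not be taken orally, intravenously, or intracoronally during the study". No period before enrolment is mentioned.

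Patient recruitment and eligibility prints the exclusions as a list. Two items look back at earlier treatment or products: thrombolysis before PCI, and taking part in another study of an investigational product or device in the last 30 days. Marketed Danhong given in routine care falls under neither. Symptoms must have been present for no more than 12 h, and "Patients will be screened for eligibility at hospital admission as soon as possible". Under Randomization, allocation follows consent.

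The Background says that "Danhong Injection has been widely applied in the treatment of coronary heart disease, angina pectoris, MI", among other conditions, since its Chinese launch in 2003.

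The arms differ in whether and when Danhong starts. The preoperative arm receives it "as early as possible before PCI and continue to the seventh day, once per day", the postoperative arm "right after PCI and continue to the seventh day, once per day", and the control arm not at all. The primary outcome is ST-segment resolution of at least 70% at 90 min after PCI.

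**The concern.** The ban shows that the authors saw background Chinese medicine as a threat to the comparison. For an outcome read 90 min after PCI, however, what matters is what the patient has received by then. The ban protects only the stretch from enrolment to that ECG. The hours between symptom onset and admission are open, and so is any earlier treatment for angina.

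A control patient who had Danhong in that window is not an untreated control. A postoperative-arm patient who had it resembles the preoperative condition. If earlier doses have an effect, both the efficacy contrast and the timing contrast move toward zero. Those are the trial's two stated aims.

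**Working it through.** **1. Inputs.** From Sample size: 336 patients, control rate about 50%, difference 20.2 points (so 70.2% on Danhong), two-sided 0.05, 80% power, 20% loss. From Randomization: 1:1:1, so combined Danhong versus control is 2:1. The share f of patients exposed before randomisation is not in the article, so a range is used.

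**2. The plan's own figure.** The article says that "a sample size of 336 participants was estimated to provide 80% power" for "an absolute difference of 20.2% between the combined Danhong group and control", "at a two-sided significance level of 0.05".
- For that 2:1 contrast, the pooled-variance formula gives 68 controls, 3 × 68 = 204 in total, and 204/0.8 = 255 after loss (282 with continuity correction). This is not 336.
- For one Danhong arm versus control at 1:1 with unpooled variance, n = (1.960 + 0.842)² × (0.50×0.50 + 0.702×0.298)/0.202² = 88.3, so 89 per arm. Then 89/0.8 gives 112 after rounding up, and 3 × 112 = 336.

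This mismatch is a separate matter. Here it means only that the combined contrast starts with more than 80% power.

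**3. Evaluable numbers.** 336 × 0.8/3 = 89.6, about 90 per arm, so about 179 Danhong patients versus 90 controls.

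**4. Dilution model (assumption, worst case).** A share f of controls had Danhong before randomisation and responds at the full 70.2%. The Danhong arms stay at 70.2%.
- Control rate: p₁ = 0.50 + 0.202f
- Difference: d = 0.202(1 − f)
- Power = Φ[(d − 1.960·SE₀)/SE₁], with SE₀ from the pooled rate and SE₁ from the separate rates

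Worked case, f = 10%: p₁ = 0.5202, d = 0.1818, pooled rate (0.5202 + 2×0.702)/3 = 0.6414, SE₀ = 0.0621, SE₁ = 0.0629. The argument is (0.1818 − 1.960×0.0621)/0.0629, about 0.96, so power is 83.1%.

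| f | Difference (points) | Power, combined vs control | Power, one Danhong arm vs control |
|---|---|---|---|
| 0 | 20.2 | 89.8% | 79.4% |
| 5% | 19.2 | 86.7% | 75.2% |
| 10% | 18.2 | 83.1% | 70.7% |
| 20% | 16.2 | 74.1% | 60.8% |
| 30% | 14.1 | 63.0% | 50.1% |

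Solving for 80% power on the combined contrast gives f = 13.7%.

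**5. Timing contrast.** If an earlier dose acts like the preoperative arm, a true preoperative-minus-postoperative difference D shrinks to about D(1 − f). The article plans no value of D, so no power can be attached.

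**The case against.** The strongest reply is that this is a condensed article and that look-back windows belong in the full protocol. Part of that stands, since the full protocol may define a window. But the article prints its exclusions as a list, includes a 30-day look-back for trial products, and states when the ban applies. Those stated rules leave the gap.

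Four stronger readings are tempting, and the article does not support them.

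- *The plan will enrol controls with Danhong on board.* The Background gives no rate of use in STEMI patients before admission. Index-event dosing must fit between onset (within 12 h) and screening at admission. Dosing outside the assigned arm between enrolment and PCI is already barred. Earlier use is possible, not shown.
- *Such patients have crossed over.* Exposure before randomisation is a baseline characteristic. Randomisation balances it in expectation, and stratification by centre limits imbalance from local prescribing habits. Sensitivity can be lost, but there is no push toward a false positive.
- *The damage cannot be repaired because Table 1 has no item for it.* Table 1 is a schedule of outcome assessments and lists no medication at all. It has a baseline entry for subject characteristics, and the case report form is not shown. Earlier use may well be recorded.
- *The power loss is serious.* The model credits every exposed control with the whole planned effect. Older use, or use of a different product, may do much less. Even so, the combined contrast, which is the primary comparison, keeps 80% power up to about 14% exposed. The lower figures belong to the single-arm comparisons, which come later in the hierarchy and start near 79%.

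What remains is that a record of earlier use identifies the exposed patients but cannot turn them into unexposed controls or into patients treated only after PCI.

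**Conclusion.** The gap in the text is real. The ban begins with the study, and no listed criterion covers earlier Danhong or other cardiac Chinese medicine. With wide routine use and an outcome at 90 min after PCI, this could dilute both main contrasts. The direction is toward no difference, and the size is unknown because the exposed share is not given.

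The calculated loss for the combined contrast (about 90% power down to 87%, 83% and 74% at 5%, 10% and 20% exposed) is an upper bound for each share. It rests on three assumptions: full effect in exposed controls, no change in the Danhong arms, and 20% loss. The point supports a cheap improvement to eligibility and baseline recording. It does not show that the primary comparison is compromised.

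**What to change.** 1. Add one exclusion, checked before randomisation in all three arms: Danhong Injection already given for the index event.
2. Add one screening question that records other recent use of Danhong or of Chinese medicine for coronary heart disease. The sponsor should justify the look-back length, because the length of the treatment course says nothing about residual effect. The answer should be taken before allocation is known, since treatment is open-label.
3. Plan a sensitivity analysis of the primary outcome that omits the patients so recorded. As the information predates randomisation, dropping them does not break the comparability of the arms.

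The cost is one eligibility line, one question and one extra analysis. Some otherwise eligible patients are lost, in proportion to how common earlier use is. If it is rare, few are lost and little dilution is avoided. If it is common, recruitment suffers more, but so would the contrasts without the rule.

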### Outcome

The primary outcome is the rate of STR ≥ 70% on surface electrocardiogram (ECG) at 90 min after PCI. The secondary outcomes are the degree of STR, TIMI flow grade, TIMI myocardial perfusion grade, LVEF, N-terminal prohormone brain natriuretic peptide, high-sensitivity C-reactive protein, and infarct size expressed as area under the curve for cardiac troponin I and for creatine kinase MB. The MACE (defined as a composite of nonfatal stroke, nonfatal MI, target lesion revascularization, urgent stent thrombosis, and all-cause death) will be recorded, as well as the hospital readmissions for heart failure or cardiac angina. Health quality will be assessed by using the 12-item Short Form Health Survey [28].

The safety outcomes include bleeding events measured with Platelet Inhibition and Patient Outcomes (PLATO) criteria within 48 h and 30 days, as well as adverse events (AEs) during the study period. Abnormal change in routine blood test results will also be monitored during the study. In addition, psychologic status and dietary patterns of patients will be collected as relevant indicators using the Hamilton Depression Scale [29] and the Food Frequency Questionnaire [30]. A study schedule and evaluation of outcomes are provided in Table 1. Centralized, blinded reviews of angiographic data and ECG recordings will be conducted by two physicians, respectively.

**Table 1 Tab1:** Outcome evaluation time points

Outcomes	Baseline	Preoperation	Postoperation (immediately)	30 min	60 min	90 min	6 h	12 h	18 h	24 h	36 h	48 h	72 h	7 d	30 d
Subject characteristics	•	–													
STR	•	–		•			–			•	–			•	–
TIMI flow grade TMPG	–	•		–											
LVEF	–									•	–			•	
cTnI, CK-MB	•	–					•							–	
NT-proBNP	•	–								•	–	•	–	•	
hs-CRP	•	–								•	–		•		
MACE	–														•
Hospital readmission	–														•
SF-12	•	–													•
Bleeding events	–											•	–		•
Adverse events	•														
Routine blood test	•	–													•
HAMD-17	•	–												•	
FFQ	•	–													

Abbreviations: *CK-MB* Creatine kinase-MB, *cTnI* Cardiac troponin I, *FFQ* Food Frequency Questionnaire, *HAMD-17* Hamilton Depression Scale-17, *hs-CRP* High-sensitivity C-reactive protein, *LVEF* Left ventricular ejection fraction, *MACE* Major adverse cardiovascular event, *NT-proBNP* N-terminal prohormone brain natriuretic peptide, *SF-12* 12-item Short Form Survey, *STR* ST-segment restoration, *TIMI* Thrombolysis in Myocardial Infarction, *TMPG* Thrombolysis in Myocardial Infarction myocardial perfusion grade

*Note*: • = essential item

### Sample size

Based on the results of the previous investigation [31–33], a sample size of 336 participants was estimated to provide 80% power to detect an absolute difference of 20.2% between the combined Danhong group and control in the rate of STR ≥ 70% measured at 90 min after PCI at a two-sided significance level of 0.05, assuming an STR ≥ 70% rate of roughly 50% for the control group and 20% loss to follow-up.

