### Randomization

In each center, the enrolled patients will be randomly assigned to the control group of conventional treatment, the preoperative-Danhong group, or the postoperative-Danhong group, allocated by the central randomized management system according to a ratio of 1:1:1. The randomization sequence will be generated in varying block sizes and stratified by center. After informed consent is obtained, the researcher will log into the central randomized management system of the network and choose the center as the stratified factor. The central randomized management system will generate a unique identification code and random number for each patient, which can be used to represent the identity of the patient and indicate the therapeutic intervention.

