### Statistical analysis methods

The null hypothesis is that the rate of STR ≥ 70% at 90 min after PCI will be the same for the combined Danhong group and the control group. The primary outcome analysis will use the Cochran-Mantel-Haenszel test to compare the rate of STR ≥ 70% at 90 min after PCI between the combined Danhong groups and the control group. If the result of this analysis is significant, hierarchical testing will be used to compare the preoperative-Danhong group with the control group, the postoperative-Danhong group with the control group, and the preoperative-Danhong group with the postoperative-Danhong group.

For other categorical variables, comparisons between treatment groups will be done using Fisher’s exact test or the chi-square test as appropriate. Continuous variables will be compared using the *t* test or Wilcoxon rank-sum test as appropriate. Chi-square or Fisher’s exact tests will be used to compare the frequency of AEs between groups.

The intention-to-treat population, including all randomized patients, will be used for all efficacy and safety analyses. All analyses will be performed using SAS version 9.4 software (SAS Institute Inc), with a two-sided *P* value less than 0.05 considered significant. No interim efficacy analysis will be performed.

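### The 80% power stated for combined Danhong versus control does not follow from its own inputs: 336 patients at 2:1 give about 90%, and 80% is about the power of one Danhong arm versus control

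*Protocol article*

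**What the plan says.** The Sample size section of the protocol article ties the patient number and the power to one named contrast: "336 participants was estimated to provide 80% power to detect an absolute difference of 20.2% between the combined Danhong group and control". The test is set "at a two-sided significance level of 0.05", "assuming an STR ≥ 70% rate of roughly 50% for the control group", and 20% of patients are expected to be lost.

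The Randomization section allocates patients to control, preoperative Danhong and postoperative Danhong "according to a ratio of 1:1:1".

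The Statistical analysis methods section makes the same pooled contrast the null hypothesis and the primary analysis: a Cochran-Mantel-Haenszel test is used "to compare the rate of STR ≥ 70% at 90 min after PCI between the combined Danhong groups and the control group". The three pairwise comparisons follow hierarchically if that test is significant. The intention-to-treat population is defined there as all randomised patients.

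**The concern.** Two Danhong arms pooled against one control arm is a 2:1 comparison, with 224 against 112 patients randomised. A pooled test of this kind has clearly more power than a single arm against control. The paragraph states all its inputs, so the 80% can be checked directly, and it does not come out.

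What is at stake is how the trial is read, not whether it is large enough. A null result on the primary test would be judged against a 20.2-point difference at 80% power, although the design has about 90% power there and reaches 80% at a smaller difference. A reader who takes 336 as sized for the pooled test would also conclude that the single arms fall well below 80%. With lost patients excluded they do not, and timing is one of the trial's stated aims.

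**Working it through.** **Inputs.** Control rate 0.500, Danhong rate 0.500 + 0.202 = 0.702, two-sided alpha 0.05, power 0.80, loss 20%, total 336 (all from Sample size); allocation 1:1:1 (Randomization). Per arm: 336 / 3 = 112 randomised and 112 × 0.8 = 89.6 evaluable. Combined Danhong: 224 randomised and 179.2 evaluable. The Cochran-Mantel-Haenszel test is approximated by the unstratified two-proportion test.

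**Step 1: reproduce 336 for the comparison named (2:1).** The unpooled formula for the control arm is n = (1.96 + 0.8416)² × [p1(1−p1) + p2(1−p2)/2] / (p2−p1)².

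7.849 × (0.2500 + 0.2092/2) / 0.0408 = 68.2, so 69. Then 69 / 0.8 = 86.25, so 87, and 87 × 3 = 261. The pooled-variance formula gives 68, and 68 / 0.8 = 85, times 3 = 255. A continuity correction raises the total to 282. None of these is 336.

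**Step 2: power of the combined test with 336 randomised and 20% excluded.**
- Unpooled: SE = √(0.2500/89.6 + 0.2092/179.2) = 0.0629. Then 0.202/0.0629 − 1.96 = 1.251, so power is 0.895.
- Pooled: the average rate is (0.500 + 2 × 0.702)/3 = 0.635 and the null SE is 0.0623. Then (0.202 − 1.96 × 0.0623)/0.0629 = 1.270, so power is 0.898.

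At 90 versus 179, exact enumeration of the chi-square test gives 0.899, Fisher's exact test 0.894 and the continuity-corrected test 0.875. Since the control rate is given only approximately, it was varied from 45% to 55% with the difference held at 20.2 points: pooled power runs from 0.888 to 0.914.

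**Step 3: difference detectable by the combined test at 80% power.** Solving the pooled formula at 89.6 versus 179.2 gives about 17.7 points.

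**Step 4: one Danhong arm versus control (1:1).** Unpooled: 7.849 × (0.2500 + 0.2092)/0.0408 = 88.3, so 89. Then 89 / 0.8 = 111.25, so 112, and 112 × 3 = 336. The pooled formula gives 92, then 115, then 345. Power at 89.6 versus 89.6 is 0.806 unpooled and 0.794 pooled.

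**Step 5: lost patients counted as non-resolved.** The rates become 0.8 × 50% = 40.0% and 0.8 × 70.2% = 56.2%, a difference of 16.2 points, with all 336 analysed. The pooled 2:1 formula then needs 112 controls, so 336 in total.

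| Handling of the 20% | Combined vs control | One arm vs control |
|---|---|---|
| Excluded (50% vs 70.2%) | about 90% | about 80% |
| Counted as non-resolved (40.0% vs 56.2%) | about 80% | about 68% |

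**The case against.** The strongest reply is Step 5. The Statistical analysis methods section analyses all randomised patients. If the 20% lost are kept in and scored as non-resolved, 336 is exactly the number needed for 80% power on the combined test. On that reading the sentence could be right about both the comparison and the power.

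Part of this stands. It shows that the pairwise calculation is not the only route to 336. That calculation also matches exactly only with the unpooled formula, and the full protocol, which the article condenses, may hold the derivation. A reader might infer that 336 was certainly sized on a single arm and the power mislabelled; the documents do not establish that.

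It does not rescue the paragraph as printed. The definition of the intention-to-treat population says who is analysed, not how a missing ECG is scored. The Sample size section gives no scoring rule and states a detectable difference of 20.2 points, whereas the difference analysed under this rule would be 16.2. Splitting alpha in three also comes close (339 patients at 2:1), but it contradicts the stated 0.05.

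Three further inferences go too far:
- **That the trial is underpowered.** On the printed inputs the primary test has more power than claimed.
- **That the missing pairwise power is itself an error.** Those tests come after the primary test, and stating power for the primary hypothesis alone is common in a condensed article.
- **That 20% loss is wrong for an ECG taken 90 minutes after PCI.** The documents give no loss figure for that ECG, so they offer nothing to put in its place.

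**Conclusion.** The point holds. For the comparison it names, the stated power is about 10 percentage points too low: about 90% (0.895 to 0.898) rather than 80%. Put the other way, 336 is 75 to 81 patients more than the 261 or 255 that 80% power would need. The discrepancy survives continuity correction and control rates from 45% to 55%.

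The conclusion rests on the usual reading of the loss allowance, that lost patients drop out of both groups equally, and on approximating the stratified test by an unstratified one. That the 80% belongs to each Danhong arm versus control is the likely explanation, not a fact in the documents.

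Severity is moderate. The error is conservative for the primary test, and the patient number, alpha and tests all stand. What is wrong is the published description of what the design can detect.

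**What to change.** Keep 336 and reword the Sample size paragraph. It should say that 112 patients per arm, about 90 evaluable after excluding 20%, give about 90% power for combined Danhong versus control at 50% versus 70.2% (two-sided 0.05, 2:1), with a difference of about 17.7 points detectable at 80% power. It should add that each Danhong arm versus control has about 80% power at the same rates.

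If the sponsor meant lost patients to count as non-resolved, the paragraph should state that rule and the analysed rates of 40.0% versus 56.2%, with power of about 80% for the combined test and about 68% for a single arm. The sponsor must say which of the two applies, because the figures differ.

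The cost is a few sentences. Enrolment, allocation and the planned tests do not change.
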